##### Intervention 2 – Fitness Instructor led group exercise

The fitness instructors be registered by the National Council for Exercise and Fitness. They will be given a standardised pack in order to document the interventions.

##### Intervention 3 – Yoga classes

Yoga instructors will be accredited by the Yoga Federation of Ireland. They will be given a standardised pack in order to document the interventions.

#### Strand B

##### Intervention 1 – Group Physiotherapy

Participants attended a weekly hour long class for 10 weeks. The circuit style class will consist of exercises that combine strength and balance. Participants will complete 6 different exercises at each class. The exercises were adapted from the falls prevention literature where similar programmes have been seen to improve, balance and reduce the number of falls in an elderly population.

The six exercises and possible progressions are described below. These are to be performed in sets of 12. When a participant is able to perform 12 repetitions of an exercise safely this can be progressed up to 3 sets of 12 repetitions. When a participant can perform 3 sets safely the exercise will be progressed so as to continuously challenge the participant. Not all participants will progress through all the exercises. The progression is dependent on the ability of the participant and their safety while performing the exercises

1. Sit to Stand, progressed by altering;

Hand Positioning – Participants may initially need to use hands for support to rise from chair, then progressing to hands by side and then to hands across chest.

Seat Height – Participants may initially require a higher seat height which can be lowered to increase the intensity of the exercise.

Repetitions – To be performed in sets of 12 and number of sets to be increased to 3 as participant progresses.

Weights – Handheld weights may be given to participants who need further progression.

2. Squat, progressed by altering;

Support – Participants may initially need bilateral support, this can be decreased to unilateral and then to no support as participants' ability increases.

Repetitions – To be performed in sets of 12 and number of sets to be increased to 3 as participant progresses.

Weights – May be given to participants who are able to perform 3 sets of 12 squats safely with no support.

3. Calf Raises, progressed by altering;

Support – Participants may initially need bilateral support, this can be decreased to unilateral support and then to independent calf raises as participant progresses.

Repetitions – To be performed in sets of 12, to be increased as participant progresses.

Other options – If participants are able they may perform single leg calf raises or if they can perform 3 sets of 12 independent calf raises weights can be added as further progression.

The following three exercises are to be completed within parallel bars.

4. Step ups, progressed by altering;

Support – Participants may begin with bilateral support, and then decrease to unilateral support, then to no support.

Stepping – Initially participants may step onto step and back to starting position, then step onto step and over, and then onto step, over and backwards to starting position.

Step Height – When participants are comfortable with all directions of stepping step height may be increased.

5. Side Stepping – progressed by altering;

Support – Participants may begin with bilateral support, and then decrease to unilateral support, then to no support.

Number of steps – Initially participants may only take one step in each direction. This can be increased as participants' ability increases.

If a participant is unable to take a step to the side, weight shifting from side to side in standing may be performed and progressed to stepping when the participant is able.

6. Tandem Stepping/Walking – progressed by altering;

Support – Participants may begin bilateral support, and then decrease to unilateral support, then to no support.

Stepping – Participants may initially just place one foot in front of the other and hold this position. The number of steps can then be increased as the participant progresses.

Crossover – Participants may become competent at tandem walking. This can then be progressed to one foot crossing over in front of the other.

##### Intervention 2 – One on one Physiotherapy

These participants will receive individual treatment depending on the problem list and goals established by the Chartered Physiotherapist who was treating them. The content of the intervention will be recorded for each individual treatment session. The duration of the individual sessions will be the same as the group led physiotherapy.

##### Intervention 3 – Yoga

Participants will attend a weekly yoga class of approximately one hour's duration. All yoga instructors will be members of The Yoga Federation of Ireland and will keep a log of the content of each yoga class.

### Statistical Analyses

All measures will be summarised and tested for normality. If variables are non-normal then Wilcoxon Signed Rank tests will be used to test for differences before and after interventions and Mann-Whitney U tests will be used to test for differences between groups before and after interventions. If the variables are reasonably normally distributed then repeated measures ANOVA will be carried out to test for differences between groups and over time. Suitable plots will be used to demonstrate the changes found.

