**Discussion:**

Data analysis will analyse change in each group, and the differences between groups. Sub group analysis may be performed if sufficient numbers are recruited.

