## Methods and design

### Design

This will be a multi-centre, prospective, single blinded, block randomised controlled trial. Participants will be stratified according to mobility level using the mobility section of the Guys Neurological Disability Scale[24]. Those who score 0, 1 or 2 are stratified to stand A, those scoring 3 and 4 to strand B. For each strand blocks of subjects will be randomised to one of the interventions or to the control group.

Strand A will concern individuals with MS who walk independently or use one stick to walk outside. The objective is to compare the immediate and long term effect of yoga, physiotherapy led exercise class, fitness instructor led exercise class to a control group who don't change their exercise habits.

Strand B will concern individuals with MS who walk with bilateral support or a rollator, they may use a wheelchair for longer distance outdoors. The objective is to compare the immediate and long term effect of 1:1 Physiotherapist led intervention, group intervention led by Physiotherapist, or group yoga intervention to a control group who don't change their exercise habits.

The study protocol was approved by 10 regional ethics committees in the Republic of Ireland

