### Assessment

Each participant will be assessed by a blinded assessor who is unaware of group allocation. Assessors will attend training days in order to standardise the measurements.

Assessments will be carried out at baseline (week 1), post-intervention (week 12) and at follow-up (week 24). The following outcome measures will be used for all three assessments: Multiple Sclerosis Impact Scale 29 version 2 (MSIS), Modified Fatigue Impact Scale (MFIS), six minute walk test (6MWT), physiological cost index (PCI), and hand held dynamometry (HHD). In addition the Berg Balance Scale (BBS) and the Modified Ashworth Scale (MAS) will be used for strand B. As equipment for PCI and HHD are not available to all assessors some participants will not have these measures recorded. The more physically demanding outcome measures were separated to avoid fatigue and so the order of testing for strand A was 6MWT including PCI, MSIS, HHD, MFIS. For strand B it was 6MWT including PCI, MSIS, BBS, MFIS, MAS, HHD

A standardised assessment at baseline considered the participants suitability for exercise and measured confounding variables such as level of sensory loss, coordination deficits etc.

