### Sample size calculations

#### Strand A

Based on a pilot study and the MSIS physical component scores then a sample size of 60 in each group will be sufficient to show a similar probability (0.329) that an observation after intervention will be less than before intervention as in the pilot study (mean before intervention 62.4, after intervention 53.6). This is based on using the Wilcoxon Signed Rank Test, significance level 0.05 and a power of 90%.

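### A normality test chooses the analysis, and neither route makes a baseline-adjusted comparison with control the primary test

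*Protocol article*

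**What the plan says.** The Statistical Analyses section opens with a gate: "All measures will be summarised and tested for normality". Two routes follow.

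- **Non-normal route, within each arm.** "If variables are non-normal then Wilcoxon Signed Rank tests will be used to test for differences before and after interventions".
- **Non-normal route, between arms.** No covariate is named here: "Mann-Whitney U tests will be used to test for differences between groups before and after interventions".
- **Reasonably normal route.** "repeated measures ANOVA will be carried out to test for differences between groups and over time".

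The abstract gives within-group change and between-group difference equal standing: "Data analysis will analyse change in each group, and the differences between groups". The Design section sets a comparative question for Strand A ("The objective is to compare the immediate and long term effect of yoga, physiotherapy led exercise class, fitness instructor led exercise class to a control") and a parallel one for Strand B. For Strand A the sample size section says "This is based on using the Wilcoxon Signed Rank Test, significance level 0.05 and a power of 90" per cent; the Strand B text names the same test, level and power. The Assessment section lists MSIS at baseline, week 12 and week 24. Under Recruitment and Randomisation, each block of 8 consenting people in a strand is allocated as a whole to one condition.

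**The concern.** Three features of the text do not serve the stated objective.

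1. The outcome data choose the method, measure by measure. The same outcome could be analysed differently in the two strands because a normality test is more sensitive at 60 per arm than at 22.
2. The non-normal route includes before-after tests inside each arm. These answer whether an arm changed, not whether it changed more than control. Placed beside a control arm with its own p-value, they invite the inference that an arm which reached significance beats a control which did not. The Mann-Whitney comparison made before the intervention can detect only chance imbalance between randomised groups, so it informs no treatment question.
3. Neither route makes a baseline-adjusted contrast with control the primary test, although the covariate is already collected. That gives up precision and leaves a chance baseline difference uncorrected in any comparison of week 12 scores.

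At stake is whether the trial's headline rests on a direct and reasonably precise comparison with control.

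**Working it through.** **The plan's own figures.** Inputs from the sample size section: probability 0.329 (A) and 0.217 (B), alpha 0.05, power 90%, n = 60 and 22 per group. With (1.960 + 1.282)² = 10.51, Noether's two-sample rank formula gives, per group, 10.51 / [6(p − 0.5)²]:
- A: 10.51 / (6 × 0.02924) = 59.9, so 60.
- B: 10.51 / (6 × 0.08009) = 21.9, so 22.

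Noether's signed-rank formula, 10.51 / [3(p − 0.5)²], gives 119.8 and 43.7 pairs. A simulated signed-rank test with normally distributed change and p read as the probability of a change in one direction has 91.7% power at 60 and 91.6% at 22. The sample sizes are therefore not called wrong here. The text names a within-arm test, while the numbers fit the two-sample formula exactly.

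**Within-arm significance when nothing works.** Assume that all four arms share a change of d SD of change, that arms are independent, and that each is tested two-sided at 5%. The documents give no value for d; 0.2 to 0.3 is assumed. Let p be the power of the one-sample test (noncentral t, noncentrality d√n). Then P(at least one of three active arms significant, control not) = (1 − p)[1 − (1 − p)³].

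| n per arm | d | p | Result |
|---|---|---|---|
| 60 | 0.2 | 0.332 | 0.668 × (1 − 0.668³) = 0.47 |
| 60 | 0.3 | 0.628 | 0.372 × (1 − 0.372³) = 0.35 |
| 22 | 0.2 | 0.146 | 0.854 × (1 − 0.854³) = 0.32 |
| 22 | 0.3 | 0.269 | 0.731 × (1 − 0.731³) = 0.45 |

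A simulated Wilcoxon test gives per-arm rates of significant improvement of 0.306 and 0.597 (n = 60) and 0.136 and 0.244 (n = 22). In the same formula these give 0.46 and 0.38, and 0.31 and 0.43, so the choice of test matters little. The drift matters: with none, at least one of three inactive arms shows significant improvement in only 7.5% (n = 60) or 8.4% (n = 22) of simulated trials, whatever the control arm shows.

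**The gate.** Assuming Shapiro-Wilk at 5% (the protocol names no test) and a moderately skewed gamma variable with shape 4, normality is rejected in 78% of samples of 60 and 32% of samples of 22.

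**Precision.** The documents give no SD and no baseline-outcome correlation, so r = 0.6 to 0.7 is assumed, with equal variances at the two visits. Relative to a week 12 score comparison (variance 1), a change comparison has variance 2(1 − r) and a baseline-adjusted comparison 1 − r².
- Adjusted against week 12 score: 1 − 0.36 = 0.64; 1 − 0.49 = 0.51.
- Adjusted against change: (1 − r²) / [2(1 − r)] = (1 + r)/2 = 0.80; 0.85.

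For illustration, take r = 0.7, a difference of 0.5 SD and no allowance for block. At 60 per arm, power is 76% for a post-score Mann-Whitney, 94% for change and 97% adjusted. At 22 per arm it is 37%, 57% and 64%.

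**Blocks.** 22/8 = 2.75, about three blocks per arm in Strand B; 60/8 = 7.5 in Strand A.

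**The case against.** Both routes contain a between-arm test, and that is the strongest reply. A Mann-Whitney test on week 12 scores between randomised arms tests the treatment effect, only less precisely. Repeated measures ANOVA keeps baseline as a time level, and its group-by-time term compares change between arms. A reader might infer that the plan discards baseline altogether or never compares change between arms. The text does not support that: it is untrue of the ANOVA route, and on the other route the wording does not settle whether Mann-Whitney is applied to scores or to changes.

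Three further inferences also go too far.
- Six pairwise tests per strand do not follow, because the Design section compares three interventions with control, which is three contrasts.
- Losing everyone with a missed visit is not stated. The article does not say how missing visits enter the ANOVA, and such rules commonly sit in an analysis plan that is not shown.
- The baseline variables described as "measured confounding variables such as level of sensory loss, coordination deficits etc" are impairments, not MSIS, so they say nothing about how baseline MSIS will be used.

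The 32 to 47% range is also conditional. It needs a drift shared by a control arm told to keep its normal routine, and investigators who would argue from within-arm results despite having a between-arm test. Nothing in the document says they would.

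A full analysis plan might name the covariates, so an incomplete list would be no finding. What stands is what the article itself fixes: the gate, the within-arm tests, the before-intervention group comparison, and two routes of which neither makes an adjusted contrast with control primary.

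**Conclusion.** The point holds in this limited form. The stated analysis is chosen by a normality test, gives within-arm tests a place they cannot justify for a comparison with control, and makes no baseline-adjusted contrast primary on either route. Valid between-arm tests do exist on both routes, so the plan is not without a treatment comparison; it is less precise than it need be and open to a misleading reading.

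The misleading pattern would arise in roughly a third to a half of null trials, but only under the assumed common drift. The precision loss depends on the route. At the assumed correlations, baseline adjustment removes 36 to 49% of the variance of a Mann-Whitney run on week 12 scores, but only 15 to 20% of that of the change contrast in the ANOVA. It would be wrong to quote the larger figure for the whole plan. The ANOVA figure treats the contrast as baseline to week 12; with three visits the overall group-by-time test is not identical to it.

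**What to change.** - Remove the normality gate and the significance tests of baseline differences.
- In each strand, make the primary analysis week 12 MSIS by allocated arm, with baseline MSIS as covariate. Allow for the blocks of 8 allocated together, using a small-sample degrees-of-freedom correction.
- Report each of the three intervention-versus-control differences with a confidence interval.
- Keep a rank-based analysis as a sensitivity analysis for non-normality.
- Report within-arm change descriptively, without p-values.

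No new data are needed. The cost is slightly more analysis work. Allowing for block may also widen the intervals, especially in Strand B with about three blocks per arm, so the power figures above, which ignore blocks, should not be read as what the revised analysis will deliver.

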**Methods and design:**

This is a multi-centre, single blind, block randomised, controlled trial. Participants will be recruited via the ten regional offices of MS Ireland. Telephone screening will establish eligibility and stratification according to the mobility section of the Guys Neurological Disability Scale. Once a block of people of the same strand in the same geographical region have given consent, participants will be randomised. Strand A will concern individuals with MS who walk independently or use one stick to walk outside. Participants will be randomised to yoga, physiotherapy led exercise class, fitness instructor led exercise class or to a control group who don't change their exercise habits.

Strand B will concern individuals with MS who walk with bilateral support or a rollator, they may use a wheelchair for longer distance outdoors. Participants will be randomised to 1:1 Physiotherapist led intervention, group intervention led by Physiotherapist, group yoga intervention or a control group who don't change their exercise habits. Participants will be assessed by physiotherapist who is blind to the group allocation at week 1, week 12 (following 10 weeks intervention or control), and at 12 week follow up. The primary outcome measure for both strands is the Multiple Sclerosis Impact Scale. Secondary outcomes are Modified Fatigue Impact Scale, 6 Minute Walk test, and muscle strength measured with hand held dynamometry. Strand B will also use Berg Balance Test and the Modified Ashworth Scale. Confounding variables such as sensation, coordination, proprioception, range of motion and other impairments will be recorded at initial assessment.

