#### Strand B

Based on a pilot study and the MSIS physical and psychological component scores then a sample size of 22 in each group will be sufficient to show a similar probability (0.217) that an observation after intervention will be less than before intervention as in the pilot study (mean before intervention 23.0, after intervention 18.8). This is based on using the Wilcoxon Signed Rank Test, significance level 0.05 and a power of 90%.

As parametric tests require less subjects for the same power these numbers should be sufficient even if these tests are used instead of the non-parametric tests given above.

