## Discussion

This multi-centre, prospective, single blinded, block randomised controlled trial aims to determine which physiotherapy or exercise intervention MS Ireland should deliver in order to reduce the impact of MS, reduce fatigue and optimise activity in people with MS. It uses the recommendations of the Cochrane review[6] by including blinded assessments, concealing allocation to groups and documenting drop outs in detail. If sufficient numbers are recruited sub-group analysis may be carried out in order to analyse which impairments are associated with success from each of the interventions, or who does best from what treatment.

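### In the non-normal branch, four arms are compared by unadjusted two-group tests: about a 12.5% chance of a false difference from control per strand on one MSIS score, with group sizes that match a single comparison

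*Protocol article*

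**What the plan says.** The Abstract of the protocol article gives the arms of Strand A: "Participants will be randomised to yoga, physiotherapy led exercise class, fitness instructor led exercise class or to a control group". Strand B likewise has three interventions and a control. The Design section sets the objective in each strand as comparing the three interventions with the control group.

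The Statistical Analyses section has two branches. For non-normal variables, signed-rank tests are used within groups, and "Mann-Whitney U tests will be used to test for differences between groups". For reasonably normal variables, repeated measures ANOVA tests for differences between groups and over time. Neither branch states a significance level, a primary contrast or an adjustment.

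The only significance level is in the sample size section, where Strand A reads "This is based on using the Wilcoxon Signed Rank Test, significance level 0.05 and a power of 90" per cent; Strand B has the same settings. Strand A is sized on the MSIS physical component, and Strand B on the physical and psychological components. The Abstract names the MSIS as primary without choosing a component.

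The Discussion says that the trial "aims to determine which physiotherapy or exercise intervention MS Ireland should deliver".

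**The concern.** Mann-Whitney handles two groups at a time. Applied to a four-arm strand, it means at least the three comparisons with control named in the objective, and up to six pairs. Each such test carries its own 5% error, and all of them inform one decision: what the provider should offer. If any of several unadjusted results can support that decision, the chance of being misled within a strand exceeds the 5% of a single test.

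This is not a remote branch. Both strands are sized on rank tests, and the sample size section treats parametric tests as the alternative that might be used instead. The choice also affects sample size, because adjusted contrasts need more participants for the same power.

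**Working it through.** **Inputs.** From the protocol article: four arms per strand with even allocation (Recruitment and Randomisation); significance level 0.05 and power 90% (Sample size calculations); planning probability 0.329 with 60 per group in Strand A, and 0.217 with 22 per group in Strand B. Assumed: two-sided tests (sidedness is not stated) and independent participants. The allocation of whole blocks of 8 is not allowed for here.

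**Step 1: reproduce the stated sizes.** Noether's formula for a two-group Mann-Whitney test is n per group = (z₀.₉₇₅ + z₀.₉₀)² / [6(p − 0.5)²], with (1.960 + 1.282)² = 10.507.

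- Strand A: 10.507 / (6 × 0.171²) = 10.507 / 0.17545 = 59.9, so 60.
- Strand B: 10.507 / (6 × 0.283²) = 10.507 / 0.48053 = 21.9, so 22.

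Both figures are reproduced. The one-sided version gives 48.8 and 17.8. The signed-rank formula, with 3 in place of 6, gives 119.8 and 43.7 pairs. The sizes therefore match one two-group comparison at two-sided 0.05, although the text names the signed-rank test.

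**Step 2: chance of at least one false significant result in a strand, all four arms equal, each test at two-sided 0.05.** Three independent tests would give 1 − 0.95³ = 14.3%. The comparisons share a control, which correlates them at 0.5 and lowers this a little. A simulation of four equal arms (1,000,000 draws) gives:

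| Tests on one MSIS score | Any false difference | Multiple of 5% |
|---|---|---|
| 3 versus control | 12.5% | 2.5 |
| 6 pairs | 20.3% | 4.1 |

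Actual Mann-Whitney tests (6,000 runs) agree. For three comparisons they give 13.0% at n = 60 and 12.1% at n = 22; for six pairs, 21.8% and 20.0%.

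Counting only false results that favour an intervention over control, three comparisons give 6.3%. The matching figure for one test is 2.5%.

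**Step 3: power at the stated sizes after adjustment.** Expected z = √(6n) × |p − 0.5|, which is √360 × 0.171 = 3.244 in Strand A and √132 × 0.283 = 3.251 in Strand B. Power per contrast is Φ(expected z − critical value).

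| Rule | Critical value | Strand A | Strand B |
|---|---|---|---|
| Unadjusted | 1.960 | 90.1% | 90.2% |
| Bonferroni over 3 | 2.394 | 80.2% | 80.4% |
| Dunnett, 3 versus control | 2.348 (simulated) | 81.5% | 81.7% |

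Holm, by simulation, gives a contrast with the planned effect about 80% power if only that intervention works, 83% if two work and 87% if all three do.

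To keep 90% power under Bonferroni, n = (2.394 + 1.282)² / [6(p − 0.5)²], which is just over 77.0 in Strand A (78 rounded up) and 28.1 in Strand B (29).

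**The case against.** The strongest reply has three parts.

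First, the Mann-Whitney tests are conditional. If the data are reasonably normal, repeated measures ANOVA tests all groups together. This stands: the figures above do not apply to that overall test. It cannot by itself say which intervention to deliver, but it is not open to the same criticism.

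Second, a condensed article may leave adjustment to an analysis plan that is not shown, and naming Mann-Whitney does not rule out a prior overall test or adjusted p-values. This stands in part. The absence of an adjustment would not be a finding alone. But the article does state the between-group procedure, it is a two-group test for a four-arm design, and the stated sizes match one such comparison.

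Third, 0.05 is given only as the sizing level, so no promised strand-wise error rate is broken. That is correct.

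A reader might go further and infer that the chance of wrongly declaring an intervention effective reaches six times 5%. The documents do not support that:

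- A multiple that large needs all six pairs tested on both MSIS components: 27.1% to 36.5%, for an assumed correlation between components of 0.9 down to 0. Nothing makes the two components co-primary, Strand A is sized on one of them, and the Design objective is comparison with control.
- Even with both components, the three comparisons with control give 17.2% to 23.5%, at most 4.7 times 5%.
- These are two-directional counts. They include interventions that look worse than control, and three of the six pairs do not involve the control at all.

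**Conclusion.** The point holds for the non-normal branch. The stated procedure fits a four-arm strand badly. On one MSIS score, the three comparisons with control carry about a 12.5% chance of at least one false significant difference, or 6.3% for false benefit against 2.5% for a single test. Testing all six pairs would raise the two-directional figure to about 20%.

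These figures assume that all arms are equal, that each test is two-sided at 0.05 and unadjusted, and that participants are independent. Carrying 0.05 over from the sizing section to each analysis test is itself an assumption, though a natural one. The group sizes of 60 and 22 contain no allowance for more than one comparison.

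**What to change.** In each strand, define the primary family as the three active-versus-control contrasts on one named MSIS score at week 12. The physical score is an obvious candidate, since Strand A is sized on it. Test these contrasts with Holm- or Dunnett-adjusted p-values at a family-wise 5%, in whichever analysis branch is used. Report active-versus-active contrasts, the other MSIS component, week 24 and the remaining outcomes as secondary estimates with confidence intervals.

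An overall Kruskal-Wallis test before the pairwise tests would be a weaker remedy. It holds the error near 5% when all four arms are equal (5.3% at n = 60 and 4.8% at n = 22 in simulation), but does not protect the remaining comparisons once one arm truly differs.

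The change needs no extra participants if lower power is accepted: about 80% to 82% per contrast under Bonferroni or Dunnett, and up to about 87% under Holm if all three interventions work. The stated 90% should be restated accordingly. Keeping 90% under Bonferroni would take 78 and 29 per group. Baseline adjustment might recover some power, but the documents give no correlation between baseline and outcome, so no such gain can be counted on.

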### Recruitment and Randomisation

Participants can be referred to the project by themselves, their carer, MSI, Chartered Physiotherapists, Neurologists, GPs or Clinical nurse specialists.

Referral will be made to the ten regional offices of MSI. A form completed over the telephone will be used to screen for exclusion criteria and to stratify according to mobility level. Participants will then be sent the information leaflet for the relevant strand and a consent form. The consent form will be returned to the regional office and consenting subjects will be coded by region, number and then strand (e.g. MW1A, MW2A, MW3B...). The participants General Practitioner will be sent a letter informing them of their participation and enclosing the relevant information leaflet. Once consent for 8 people of a strand is obtained, the regional office will contact the National Coordinator who will allocate that block of subjects to the control or an intervention condition. Block randomisation was done using a sealed enveloped with pieces of paper with the four groups written on them. The paper chosen will be emitted each time until four groups are chosen to ensure even numbers of groups. When the fifth group is ready to go, all the pieces of paper will be returned to the envelope, and so on. The order of allocation to control or intervention will be concealed from the regional offices until they have scheduled that block of 8 people for assessment.

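### The planned between-group tests use none of the baseline impairments or the within-strand mobility score, so precision is given up and chance imbalance, mainly in Strand B, goes uncorrected

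*Protocol article*

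**What the plan says.** Two places in the protocol article describe baseline variables as confounders. The abstract's methods paragraph says: "Confounding variables such as sensation, coordination, proprioception, range of motion and other impairments will be recorded at initial assessment". The Assessment section says that the standardised baseline assessment "measured confounding variables such as level of sensory loss, coordination deficits etc".

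Mobility is known for everyone. Under Recruitment and Randomisation, "A form completed over the telephone will be used to screen for exclusion criteria and to stratify according to mobility level". The Design section turns the score into two strands: "Those who score 0, 1 or 2 are stratified to stand A, those scoring 3 and 4 to strand B". Within a strand the score therefore still takes three values in A and two in B.

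Statistical Analyses names three methods. For non-normal variables, change within a group is covered first: "Wilcoxon Signed Rank tests will be used to test for differences before and after interventions". The arms are then compared by a separate rank test: "Mann-Whitney U tests will be used to test for differences between groups before and after interventions". If they are reasonably normal, "repeated measures ANOVA will be carried out to test for differences between groups and over time". No covariate appears in any of them.

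The only stated analytic use of the impairments is in the Discussion, conditional on recruitment: "sub-group analysis may be carried out in order to analyse which impairments are associated with success from each of the interventions".

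**The concern.** A variable that a plan calls a confounder is one that the comparison is expected to take into account. Here the plan collects such variables and then names between-group methods that leave them out. It is not merely silent: it commits to a method, and in the non-normal branch that method cannot be adjusted.

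Two things are at stake. First, precision: variance in MSIS that baseline variables could explain stays in the error term. Second, conditional accuracy: if two arms happen to differ on mobility or an impairment that predicts MSIS, the unadjusted contrast carries that difference. The design makes such differences larger than usual, because whole blocks of 8 people from one region go to one condition and each arm holds few blocks.

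**Working it through.** **1. The plan's own sample sizes.** Inputs from Sample size calculations: 60 per group with probability 0.329 (Strand A), 22 per group with probability 0.217 (Strand B), significance level 0.05, power 90%. Noether's two-sample formula, two-sided, is n per group = (1.960 + 1.282)² / (6(p − 0.5)²).
- A: 10.507 / (6 × 0.171²) = 59.9
- B: 10.507 / (6 × 0.283²) = 21.9

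Both stated figures reproduce, so the sizes fit an unadjusted two-group rank test with no covariate gain assumed. The text itself names a signed-rank test and a before-after probability. That mismatch is a separate matter; it is noted because step 4 reads 0.329 as a two-sample probability.

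**2. Chance imbalance.** Blocks per arm are 60/8 = 7.5 in A and 22/8 = 2.75 in B, taken as 8 and 3 whole blocks. The block ICC of a baseline covariate is not in the document; 0.05 is assumed, with range 0 to 0.10. For a standardised covariate, the SD of the difference between two arms is √(2(1 + 7 × ICC) / (8 × blocks)). The chance of a difference beyond 0.5 SD is the two-sided normal tail at 0.5/SD.

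| Strand | ICC | SD of difference | 0.5/SD | Probability beyond 0.5 SD |
|---|---|---|---|---|
| A | 0 | 0.177 | 2.83 | 0.5% |
| A | 0.05 | 0.205 | 2.43 | 1.5% |
| A | 0.10 | 0.230 | 2.17 | 3.0% |
| B | 0 | 0.289 | 1.73 | 8% |
| B | 0.05 | 0.335 | 1.49 | 14% |
| B | 0.10 | 0.376 | 1.33 | 18% |

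These are for one covariate and one pair of arms. If the covariate had a partial correlation of 0.3 with the outcome (an assumption), a 0.5 SD imbalance would move the contrast by 0.3 × 0.5 = 0.15 SD.

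**3. Precision.** If the added covariates explain a further share R² of outcome variance, the gain in effective sample size is 1/(1 − R²) − 1. The document gives no covariate-outcome correlation, so R² is shown as a range.

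| R² (assumed) | Gain | 60 acts like | 22 acts like |
|---|---|---|---|
| 1% | 1% | 60.6 | 22.2 |
| 5% | 5% | 63.2 | 23.2 |
| 10% | 11% | 66.7 | 24.4 |
| 20% | 25% | 75.0 | 27.5 |

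**4. What this means for power, as an illustration in Strand A.** Reading 0.329 as a two-sample probability under normality, d = √2 × z(0.671) = 0.626. Take a true effect of 70% of that, 0.438. Power is Φ(0.438 / √(2 × DE × (1 − R²)/60) − 1.960), where DE is 1 without clustering and 1 + 7 × 0.05 = 1.35 with it. The second row assumes that adjustment reduces variance within and between blocks in the same proportion.

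| | R² = 0 | 1% | 5% | 10% | 20% |
|---|---|---|---|---|---|
| Ignoring blocks | 67% | 67% | 69% | 72% | 77% |
| Block ICC 0.05 | 54% | 55% | 56% | 59% | 64% |

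The gain runs from almost nothing to about 10 percentage points. In this illustration the loss from blocks (67% to 54%) exceeds the largest gain shown from adjustment, so a model that adds covariates but ignores blocks would miss the larger problem.

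**The case against.** The strongest case on the other side is that this is mostly silence. Covariate choice is commonly left to a statistical analysis plan, the article is condensed, and an unadjusted comparison of randomised arms is a legitimate primary analysis. That stands in part: the absence of a covariate list is no finding. What remains is that the article names its between-group test, and where that is Mann-Whitney, an adjusted primary analysis would depart from the stated method.

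A reader might infer more than the text supports, in four ways.
- **That no planned test could use these variables.** Repeated measures ANOVA can take mobility as a between-subject factor or be extended with covariates. The text simply states it without them. Its group-by-time term also already removes baseline imbalance in MSIS itself.
- **That the collected variables are idle.** Mobility defines the strands, which have their own arms and sample sizes; only its variation within a strand goes unused. The impairments come from an assessment that also judges suitability for exercise, and they have a conditional subgroup use. That use asks who responds, however, and does not adjust the arm comparison.
- **That the result would be biased.** Chance imbalance after randomisation is part of the test's error rate. It does not bias the estimator and does not by itself inflate type I error. Allocation by whole blocks is a separate issue.
- **That imbalance on some covariate is more likely than not.** With five independent covariates in Strand B the chance that at least one exceeds 0.5 SD would be 1 − (1 − 0.136)⁵ = 52%. Sensation, proprioception and coordination may well be correlated, which lowers this: about 43% to 35% at assumed pairwise correlations of 0.5 to 0.7. In Strand A the corresponding figure with independence is only 7%.

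It is also fair that the article does not say how the impairments are scored or show that they predict MSIS. Much of their effect may be carried by baseline MSIS, so the further gain may be small.

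**Conclusion.** The point holds as a matter of precision and conditional accuracy, not of validity. The stated between-group analyses leave out baseline variables that the trial collects and itself calls confounders, together with the mobility score within strand. No invalid test follows from this alone.

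Large chance imbalance is mainly a Strand B concern (step 2); in Strand A the case rests almost wholly on precision. These figures depend on rounding to whole blocks and on the assumed ICC. The size of the precision gain cannot be fixed from the document and is negligible if the covariates add little to baseline MSIS. The change is worth making because it is cheap, not because the loss is known to be large.

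**What to change.** In Statistical Analyses, make the primary between-arm comparison of MSIS in each strand a regression of post-baseline MSIS on arm, with these terms:
- baseline MSIS;
- the mobility score within strand (0, 1 or 2 in A; 3 or 4 in B);
- at most one or two of the recorded impairments, named in advance;
- a term or variance method that accounts for the block of 8.

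Fix the list before any outcome data are seen and use it for every arm comparison. Do not choose covariates by testing for baseline imbalance. Keep the unadjusted result as a supporting analysis.

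The cost is wording and a little programming, with no new data. The downside is a few degrees of freedom. It matters most in Strand B, where 3 blocks in each of four arms give 12 blocks and leave 12 − 4 = 8 degrees of freedom between blocks, so the list must stay short.
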